## Analyses

### Quantitative Data

The focus is on the long-stay care setting with the resident as the unit of analysis. Analyses is by intention to treat, with all available data included. Quantitative data is analysed, in aggregate, using the Statistical Package for the Social Sciences (SPSS, v17). Data is entered into SPSS, coded and cleaned. Demographic characteristics of staff and of residents are described using percentages, measure of central tendency (means or medians) and measures of variation (standard deviations or ranges). Differences in mean scores are examined using analysis of variance and 2-sample independent t-tests. Relative risks with 95% confidence intervals are calculated with the control group as the reference. Multi-level modelling is used to address the issue of clustering within randomised groups.

Analysis of covariance is used to adjust for baseline differences in outcome variables. Test statistics based on chi-square are divided by the design effect while test statistics based on the t-test or z-tests are divided by the square root of the design effect. Whilst every effort is made to exclude all confounders at the design phase of the study, this may not always be possible. The analysis of data will, therefore, include the search for and control of nuisance variables, for which adjustments had not been made. The change in the primary response variable is modelled across the within subject factors (T_1 _and T_2_), adjusting for explanatory variables as required.

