**Figure 1 F1:**
[figure not shown]
**DARES Methodology**.

We used methods for standard sample size estimates for trials that randomised at the level of the individual [24] adjusting for clustering by inflating sample size estimates by the design effect given by $1+(\bar{n}\text{-1})\rho$, $\bar{n}$ where is the average cluster size, and ρ is the estimated intraclass correlation coefficient (ICC) [25]. Sample size estimates are based on the primary outcome of quality of life of people with Alzheimer's disease as measured by the Quality of Life-Alzheimer's disease (QOL-AD) scale. This instrument consists of two versions; one completed by the person with dementia (care recipient) and the other by the caregiver [26,27]. We chose the care recipient version to estimate sample size for the DARES trial, expressed as the mean rate difference between intervention and control groups.

Based on a mean QOL-AD score of 32.5 for people with dementia in residential care homes [28] and an ICC value of 0.1 identified from pilot work on reminiscence groups for people with dementia for the REMCARE Trial [29], a total of 18 residential units are required, each containing 17 people with dementia, to detect a 4 point difference in mean QOL-AD scores between control and experimental groups, for power of at least 80% with alpha levels of 0.05. This calculation allows for a loss to follow-up of 20% of residents and up to 3 residential units. ICC values lower than 0.1 would increase the power of the study.

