### Randomisation

Randomisation to control and intervention is at the level of the long-stay residential unit. The random allocation sequence is generated using a computer generated random number list (the Mersenne Twister, Stat Direct). Randomisation is 1:1 ratio and is stratified by public and private residential units to ensure an appropriate representation of public and private facilities; a ratio of one third public to two thirds private reflects the overall distribution of beds in the region. Concealment of group allocation is achieved by giving the responsibility for sequence generation and group allocation to a researcher with statistical expertise who is independent of the study and its investigators.

The independent statistical researcher will create a consecutive list of 12 unnamed private units, numbered 1-12, and a separate list of 6 unnamed public units, numbered 1-6. A random allocation sequence is generated and each unnamed unit is assigned a trial allocation based on the sequence. As participatory units agree to enter the trial, the research team will provide the independent statistical researcher with an anonymised list of unit(s) that meet the eligibility criteria. The independent statistical researcher will then document the unique identification code assigned to that unit in the next 'unnamed' position in the randomised public or private list and release the corresponding group allocation for the unit.

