### Blinding

This is a single-blind cluster randomised trial. Resident and staff participants within each participating unit are recruited, and baseline data collected, prior to the random allocation of units to control and intervention groups. Because of the nature of the intervention, it is not possible to blind participants (residents with dementia or staff working in the units) to group allocation. Outcome assessment is protected by blinding the research nurses involved in data generation and collection to the group allocation of participating units, staff and residents. Data analysis is undertaken by researchers and statisticians blinded to group allocation by providing a database of outcomes identifiable only by number.

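### The plan prescribes a post hoc search for covariates in the primary-outcome model and does not make the result secondary, so the headline estimate depends on choices made from the trial data

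*Protocol article*

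**What the plan says.** All of the relevant analysis text is in the protocol article, Analyses, Quantitative Data.

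- One adjustment is named in advance: "Analysis of covariance is used to adjust for baseline differences in outcome variables".
- After conceding that design may not remove every confounder, the section says: "The analysis of data will, therefore, include the search for and control of nuisance variables, for which adjustments had not been made".
- The next sentence models the change in the primary response from T1 to T2, "adjusting for explanatory variables as required".

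Two other sections bear on this. Under Randomisation, "Randomisation is 1:1 ratio and is stratified by public and private residential units", but the analysis section does not name that stratum as a covariate. Under Blinding, "Data analysis is undertaken by researchers and statisticians blinded to group allocation by providing a database of outcomes identifiable only by number".

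The Quantitative Data section does not say which variables are candidates, how they are selected, whether they must be baseline variables, or whether the resulting model is primary or exploratory.

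**The concern.** In a randomised trial the covariates of the primary model should be settled before outcomes are seen, because the significance level is guaranteed only for an analysis that does not depend on the result. Here the article commits the analysts to a search and leaves adjustment of the primary response open. This is a stated procedure. It is more than a detail held over to an analysis plan, and a plan that closed the covariate list would have to depart from the published sentence.

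The reason given for the search is weak. Baseline data are collected before units are allocated (Blinding; Outcomes), so if allocation was sound, any baseline difference between arms is chance imbalance. Variables thought likely to predict QOL-AD can be named beforehand.

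Two things are at stake. If covariates are chosen with the treatment contrast in view, the type I error rises and the estimate moves. If a variable that the intervention can change were admitted, the effect estimate would be biased. With 18 units there are 18 - 2 = 16 between-unit degrees of freedom for the arm comparison, and each unit-level covariate uses one of them.

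**Working it through.** **1. The design figures.** The sample-size text says "a total of 18 residential units are required, each containing 17 people with dementia". Its target is a difference of 4 QOL-AD points, with 80% power or more and alpha 0.05. It uses "an ICC value of 0.1 identified from pilot work on reminiscence groups".

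- Residents: 18 × 17 = 306, matching the article.
- Design effect: 1 + (17 - 1) × 0.1 = 2.6.
- Effective number per arm: 9 × 17 / 2.6 = 58.85.
- The article gives no SD, so the stated power cannot be reproduced directly. With no loss to follow-up and a two-sided test (assumed), 80% power needs an SD of at most 4 × √(58.85/2) / (1.960 + 0.842) = 7.74.

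The point does not rest on the power figure. The SD is used only to scale step 4.

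**2. Type I error if the most favourable model is taken (assumed worst case).** Null simulation on 18 unit means (9 v 9), independent unit-level covariates, smallest p-value over all models with 0 to 2 covariates. The first two columns have covariates unrelated to outcome; the third has each covariate correlated 0.3 with outcome.

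| Candidates | 2,000 runs | 3,000 runs | Correlation 0.3 (3,000 runs) |
|---|---|---|---|
| 3 | 0.089 | 0.086 | 0.103 |
| 5 | 0.120 | 0.110 | 0.163 |
| 8 | 0.169 | 0.156 | not run |

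With every subset allowed rather than at most two covariates, 5 candidates gave 0.114 (unrelated) and 0.212 (correlation 0.3).

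**3. Type I error under other rules.**

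- Covariate set fixed in advance (1, 3 or 5 covariates): 0.049-0.054.
- Selection by association with the outcome, blind to arm: 0.046-0.051.
- Adjustment only for resident-level covariates imbalanced between arms at p<0.10 (assumed 14 residents per unit, ICC 0.1, covariate ICC 0.05; 3, 5 or 8 candidates; 1,000 runs per scenario): 0.029-0.055.
- Smallest p-value over resident-level covariates in the same set-up: 0.056, 0.051 and 0.071 with 3, 5 and 8 candidates unrelated to outcome; 0.099-0.204 when each has coefficient 0.3.

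The Monte Carlo standard error near 0.05 is √(0.05 × 0.95 / 2000) = 0.005 for 2,000 runs and √(0.05 × 0.95 / 1000) = 0.007 for 1,000.

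**4. How far the estimate can move.** With 5 unit-level candidates, the median gap between the highest and lowest estimate across models was 0.35 (unrelated) to 0.52 (correlation 0.3) SDs of a unit mean. The SD of a unit mean is SD × √(2.6/17) = 0.391 × SD. Assuming a resident SD between 6 and 7.7:

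- low end: 0.35 × 0.391 × 6 = 0.8 points;
- high end: 0.52 × 0.391 × 7.7 = 1.6 points.

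The target difference is 4 points. These gaps assume no baseline adjustment, which the plan does include and which would narrow them.

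**The case against.** The strongest reply is that the article ties the search to confounders that design could not exclude. That reads as a response to imbalance in pre-existing characteristics, not as choosing covariates by their effect on the treatment p-value. Under imbalance-based selection, or selection blind to the contrast, step 3 shows no inflation. This stands. A reader might infer that the plan raises the type I error to 9-17%, or that it licenses picking the preferred result. The documents do not support that: no section prescribes choosing by p-value, and the number of candidates, their level and their correlation with outcome are all assumed.

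A reader might also infer that the plan intends to adjust for variables arising after randomisation, such as changes in care plans or T2 agitation scores. It does not say so. It only fails to exclude them, and the word confounder points toward pre-existing differences.

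On blinding, analysts who do not know which code is the intervention cannot knowingly steer toward benefit. That is a real safeguard, but a partial one. The size and p-value of the contrast between the two codes remain visible under every model, and a two-sided error rate is inflated whichever code is favoured.

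Finally, covariate lists are often left to an analysis plan, and the phrase about adjusting as required is, by itself, ordinary condensed wording. That is fair for the phrase alone. It does not answer the sentence before it, which positively prescribes a search. Intention to treat, adjustment for the baseline outcome and multilevel modelling are already stated, so only the additional covariates are open.

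**Conclusion.** The point holds as a should-fix. The article prescribes a search for covariates and open-ended adjustment of the primary response, does not confine candidates to baseline variables, and does not mark the result as secondary. The headline estimate therefore depends on covariates chosen from the trial data.

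The harm cannot be given as a single number, because the selection rule is not stated. It runs from none (type I error near 5% when selection ignores the contrast) to an assumed worst case of roughly 9-17% with 3 to 8 unit-level candidates unrelated to outcome. The worst case is higher if the candidates are prognostic, and lower for resident-level candidates that are not. The finding rests on the wording, and the simulations only show the size of the risk. The degrees-of-freedom cost applies to unit-level covariates only.

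**What to change.** Replace the search sentence and the open-ended adjustment clause with text to this effect:

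- The primary analysis is a multilevel model for QOL-AD at T2 with a random effect for unit, adjusted for baseline QOL-AD and the public/private stratum, plus any other baseline covariates listed by name before the outcome data are seen.
- No variable measured after randomisation enters the primary model.
- Any adjustment found by searching the data is reported as a labelled exploratory sensitivity analysis and cannot replace the primary result.

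The cost is one or two sentences, settled before outcome data are examined. The stratum uses one between-unit degree of freedom (16 to 15). The trial gives up the freedom to adjust the headline estimate for an unforeseen imbalance. That is a small loss, since the sensitivity analysis still shows what such adjustment would do.

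### The primary outcome is tied to a T1-to-T2 change model that is generally less precise than the ANCOVA also planned, and no single analysis is named as decisive

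*Protocol article*

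**What the plan says.** All three analyses appear in the protocol article, Analyses, Quantitative Data:

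- Means without a baseline term: "Differences in mean scores are examined using analysis of variance and 2-sample independent t-tests". The t and z statistics are later divided by the square root of the design effect.
- Baseline-adjusted: "Analysis of covariance is used to adjust for baseline differences in outcome variables".
- Change: "The change in the primary response variable is modelled across the within subject factors", the factor levels being T1 and T2, with explanatory variables added as needed.

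Multilevel modelling is named for clustering, and the analysts may also look for further variables to adjust for. The change sentence is the only analysis sentence that names the primary variable. No order is set among the three.

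The sample-size text under Methods/Design sizes the trial "to detect a 4 point difference in mean QOL-AD scores between control and experimental groups", which is a difference in means and not in changes. The Blinding and Outcomes sections place the T1 measurement before allocation. The Randomisation section stratifies by public and private unit.

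**The concern.** When T1 and T2 are levels of a within-subject factor, T1 is a response and cannot also be the baseline covariate. The change model and the ANCOVA are therefore different analyses of the same score. Change fixes the baseline slope at 1, whereas ANCOVA estimates it. Because T1 is measured before allocation, ANCOVA is fully available, and choosing change generally gives up precision without gaining anything.

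Two further things are at stake. With few units, the arms can differ at baseline by chance, and a change score over-corrects for that difference. And where several analyses of one outcome are stated without rank, the result can depend on which one is put forward. Masking the analysts to group labels does not remove this, because two-sided p-values do not depend on the labels.

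**Working it through.** **1. The plan's own sample size.** Inputs from the sample-size text: "a total of 18 residential units are required, each containing 17 people with dementia", giving 18 × 17 = 306; "an ICC value of 0.1 identified from pilot work on reminiscence groups"; "for power of at least 80% with alpha levels of 0.05" (two-sided assumed); a 4-point difference; loss of 20% of residents and up to 3 units. A mean of 32.5 is given but no SD, so the figure cannot be reproduced exactly. It can be solved for the SD.

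- After losses: 15 units × 13.6 residents (17 × 0.8) = 204, or 102 per arm.
- Design effect: 1 + 12.6 × 0.1 = 2.26. Effective n per arm: 102/2.26 = 45.1.
- Power for a T2-only comparison is 80% at SD 6.78, 88.6% at SD 6 and 77.5% at SD 7.

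The stated size is thus attainable for plausible SDs. SD 6.78 is used below as the value at which a T2-only test just reaches 80%.

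**2. Precision.** With equal variances at T1 and T2 and correlation r, relative to a T2-only comparison:

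- change: 2(1 − r)
- ANCOVA: 1 − r²
- ratio, change to ANCOVA: 2(1 − r)/(1 − r²) = 2/(1 + r)

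The article gives no r, so the values are assumed. Power uses effective n 45.1 per arm, SD 6.78 and a normal approximation.

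| r | change | ANCOVA | ratio | power, change | power, ANCOVA |
|---|---|---|---|---|---|
| 0.3 | 1.40 | 0.91 | 1.54 | 66% | 84% |
| 0.5 | 1.00 | 0.75 | 1.33 | 80% | 90% |
| 0.7 | 0.60 | 0.51 | 1.18 | 95% | 97.5% |
| 0.8 | 0.40 | 0.36 | 1.11 | – | – |

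The table takes r to be the same within and between units.

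**3. Which r.** Arms are compared largely through unit means. As an illustration, assume ICC 0.1, 17 residents per unit, within-unit correlation 0.5 and unit-level correlation 0.9.

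- Variance of a unit mean: 0.1 + 0.9/17 = 0.1529.
- Covariance: 0.1 × 0.9 + (0.9 × 0.5)/17 = 0.1165.
- Correlation of unit means: 0.1165/0.1529 = 0.76. Ratio: 2/1.76, about 1.13 to 1.14.
- The resident-level correlation is 0.1 × 0.9 + 0.9 × 0.5 = 0.54, which would give 2/1.54 = 1.30.

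So the penalty can sit at the lower end of the range. The baseline slope must also suit that level. For a slope b applied to unit means the relative variance is 1 + b² − 2b × 0.76. This is 0.48 at b = 1 (change), 0.49 at b = 0.5 (the within-unit slope) and 0.42 at b = 0.76 (the unit-mean slope). In this illustration a slope driven only by within-unit data would gain nothing over change.

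**4. Baseline imbalance.** With 18 units of 17 there are 153 residents per arm, design effect 1 + 16 × 0.1 = 2.6 and effective n 153/2.6 = 58.8. At SD 6.78 the standard error of the baseline difference is 6.78 × √(2/58.8) = 1.25 points. Given an imbalance d, the change estimate is shifted by (1 − r)d in the opposite direction. At r = 0.5 that is 0.5 × 1.25 = 0.6 points for a one-SE imbalance and 0.5 × 1.96 × 1.25 = 1.2 points for a 1.96-SE imbalance, against a target of 4.

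**5. Selection.** 20,000 null trials were simulated per r, comparing 9 with 9 unit means, each test at 5%:

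| r | any of the three | change or ANCOVA |
|---|---|---|
| 0.3 | 9.8% | 8.1% |
| 0.5 | 9.6% | 7.4% |
| 0.7 | 9.9% | 6.7% |
| 0.8 | 10.3% | 6.5% |

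Each test alone rejected in 4.8% to 5.4% of trials.

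**The case against.** The section can be read as layered: ANCOVA for baseline, multilevel modelling for clustering, and a last sentence about change that allows covariates. Change regressed on T1 gives the same treatment effect as ANCOVA, and a repeated-measures model with a common baseline mean is about as precise. This has force, but the text states neither and describes T1 as a within-subject level. The precision point is therefore conditional on the plain reading.

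The precision and selection complaints also pull apart. If the change sentence fixes the primary model, there is no open choice; if the choice is open, the change model is not the primary one. Either reading leaves a fault, but the two should not be added together.

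A journal article may leave the naming of a primary analysis to a statistical analysis plan that is not shown. That is fair, and missing rank alone would not be a finding. What remains is that the article itself attaches a change model to the primary variable alongside a generally better analysis.

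Four stronger readings are tempting, and the documents do not support them:

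- *The trial's type I error is 10%.* That holds only if the best of three results is reported, and nothing says it will be.
- *Baseline adjustment is absent.* ANCOVA is planned for the outcome variables.
- *The t-tests ignore clustering.* They are corrected by the design effect; only the baseline term is missing.
- *The promised power is lost.* The sample size takes no credit for baseline. Against a T2-only test, change is worse only if r is below 0.5, and it is unbiased over randomisation; the shift in step 4 is conditional on imbalance.

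**Conclusion.** The point holds in a limited form. The only model tied to the primary variable is a T1/T2 change model. On its plain reading it is less precise than an ANCOVA whose slope is estimated at the level that drives the comparison, for any r below 1. The variance ratio is about 1.1 to 1.5 for assumed r of 0.8 to 0.3 with equal variances, and probably nearer the lower end if unit means are stable over time. The change estimate also responds to chance baseline imbalance among 18 units. Stating three unranked analyses of one score permits selection, which would bring type I error to about 10% if it occurred. The correlations, the SD of 6.78 and the two-sided test are assumptions. The improvement is worth making because it needs nothing that the trial does not already hold.

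**What to change.** Name one primary analysis: T2 QOL-AD score in a multilevel model with arm, T1 QOL-AD score, public/private stratum and a random unit intercept. Label the T1/T2 change model and the t-tests/ANOVA as supportive, so that they do not decide the result. Given step 3 of the working, the authors may also consider adding the unit mean of T1 as a covariate, so that the baseline slope can differ between and within units. Small-sample degrees of freedom for 18 units are a separate point.

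The cost is analysis wording only. T1 scores and the stratum are already collected, and neither the sample size nor the visit schedule changes.

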### Qualitative Data

The DARES study includes an embedded qualitative component. This work is done in three parts to:

1) Support the development of the structured education programme. There have been 18 interviews with nurses and health care assistants, 9 interviews with recognised experts in the field of dementia, 3 interviews with people with dementia and 3 interviews with relatives completed.

2) Understand participants' (staff and people with dementia) perceptions of reminiscence, its impact on their lives and their experience of care. There are 9 interviews with nurses, 9 interviews with health care assistants and 9 interviews with people with dementia in the intervention group.

3) Understand and define usual care in the control sites. There are 9 interviews with clinical nurse managers in the control sites.

The primary method of data collection for the qualitative work is in-depth one-to-one interviews, guided by an interview schedule. Contextual data will have already been collected by the RNs during data collection visits to the various sites. This data will help to set the context for the relevant qualitative interviews at these sites. Grounded theory is used to guide the design of the qualitative elements of the study. The constant comparative technique is used to analyse data. Information generated at each data collection point is analysed in full prior to moving to the next stage. This approach enables data analysis to guide ongoing data collection and sampling decisions (theoretical sampling). The qualitative evaluation of residents' experiences of receiving the intervention and their understanding of the intervention will also assist in minimizing threats to fidelity.

